## Abstract

**Background:**

Dance for Parkinson’s Disease (DfPD) is a dance program for individuals with Parkinson disease (PD). There is a lack of knowledge about the effect of this program on frailty and sarcopenia experienced by patients with PD. In addition, no randomized controlled trial to date has investigated either the possible differential effects of in-person versus online DfPD or the possible effects of DfPD on clinical parameters in Greek patients with PD.

**Objective:**

We aimed to assess the efficacy, safety, and feasibility of a culturally tailored and patient-centered DfPD program offered both in-person and online to Greek patients with early- to midstage PD.

**Methods:**

This is a 3-arm crossover randomized controlled trial (in-person DfPD vs online DfPD vs control) of UPGRADE-PD (Upbeating Greek Application of Dance in Parkinson’s Disease). The experimental period will be 10 months, including three 2-month interventional periods of two 60-minute dance classes per week for each group (in-person DfPD vs online DfPD) versus a control group (nonintervention group), and two 2-month washout periods between each group for 40 Greek patients with early- to midstage PD. Assessments will be performed face-to-face at baseline and at the end of each study period and will include quality of life, fatigue, depressive symptoms, stress, anxiety, sarcopenia, frailty, balance, cognitive functions, movement and nonmovement PD symptoms, and BMI. Safety, feasibility, and patient satisfaction for each dance intervention (in-person DfPD vs online DfPD) will be assessed as well.

**Results:**

The study protocol was approved by the Medical Ethics Committee of the Eginition University Hospital in September 2022 and the Research and Ethics Committee of the University of West Attica in October 2023 and funded in September 2023. The first participant was enrolled in April 2023, and the trial is currently ongoing and will conclude in September 2024.

**Conclusions:**

The results of this study are expected to show the possible differential effect of a patient-centered and culturally tailored in-person vs online DfPD intervention on several movement and nonmovement symptoms, as well as on quality of life, sarcopenia, and frailty in people living with PD in Greece.

**Trial Registration:**

ClinicalTrials.gov NCT06220084; https://clinicaltrials.gov/study/NCT06220084

**International Registered Report Identifier (IRRID):**

DERR1-10.2196/65490

## Introduction

### Background

Parkinson disease (PD), an idiopathic, neurodegenerative, and progressive movement disorder, is accompanied by movement and nonmovement symptoms, such as bradykinesia, postural instability, and cognitive and mood disorders, which all negatively affect the quality of life (QoL) [1]. Furthermore, all the aforementioned PD symptoms seem to relate to the reduction of physical activity, muscle mass, and strength levels, as well as movement performance of patients with PD, thus increasing sarcopenia and frailty [2-4]. It is well accepted that systematic physical exercise enhances neuroplasticity [5]; prevents or delays frailty [4,6]; and improves symptoms such as balance, gait, and QoL in people with PD [7].

In dance, the human body and its purposefully selected movements are the basic tools for expression in various rhythmical and cultural contexts, whether artistic, educational, training, recreational, therapeutic, or religious [8,9]. As an art form expressed through movement, dance is a physical activity accompanied by musical stimuli that seems to activate the reward system [1] and has the potential to improve QoL of participants across various age groups [10], while the targeted use of auditory rhythmical information itself seems to be therapeutic for movement and nonmovement symptoms, as well as for QoL, in people with PD [11].

Humans, as social animals, have a fundamental need to belong [12], and dance-based interventions seem to reduce social isolation and loneliness among older people [13], while also facilitating their social inclusion [14], even during the social isolation caused by the COVID-19 pandemic [15]. Positive memories directly connected with dance experiences from a young age, as well as the supportive nature of dance, which enhances social interaction, and the emotional experiences that accompany the dance process, may be some of the reasons older adults prefer dance to other physical activities [16-18].

While physical exercise seems to induce neuroplasticity in people with PD [5], dance has been associated with favorable changes in the corticospinal tract, the corpus callosum, the superior longitudinal fasciculus, the dorsolateral prefrontal cortex, the bilateral putamen, the mirror neuron system, and sensorimotor pathways of healthy dancers [9,19]. Following the aforementioned effects of dance in neuroplasticity, dance in PD seems to enhance psychological flexibility (thus the person tends to adapt to environmental changes more efficiently) and creative self-efficacy (thus the person tends to think creatively and execute these thoughts) [20]. Dance, compared to other types of exercise, improves PD symptoms, such as balance, functional mobility, and cognition [21-24]. Moreover, dance is a substantial motivational means of exercise for patients with PD, enhancing their adherence rates to exercise programs [25,26], as well as a safe, feasible, and enjoyable intervention for patients with early- to midstage PD [27], even when the classes are remotely conducted [28].

Dance for Parkinson’s Disease (DfPD) is a structured dance program under appropriate care and supervision especially designed for people with PD, which integrates different dance genres [29]. Various studies have already described the content of the DfPD class that was followed [30-32]. To our knowledge, there is no published study investigating the effect of DfPD on the frailty and sarcopenia experienced by patients with PD. In addition, no randomized controlled trial to date has been conducted to investigate either the effect of this program on any clinical parameter in Greek patients with PD or the possible differential effect of in-person versus online DfPD. Furthermore, there is no published protocol of any patient-centered or culturally tailored dance intervention for the PD population showing the exact methodology that was followed and the content of the dance intervention. This study aims to fill the above gaps by publishing all the aforementioned data of our research protocol.

### Objective

The primary aim of this study is to investigate the possible effectiveness of a patient-centered and culturally tailored dance intervention delivered both in-person (in-person DfPD) and remotely (online DfPD) on QoL of Greek patients with early- to midstage PD. The key secondary aim is to investigate the safety and feasibility of the aforementioned interventions (ie, in-person DfPD and online DfPD) and its possible effectiveness on fatigue, depressive symptoms, stress, anxiety, sarcopenia, frailty, balance, cognitive functions, movement and nonmovement PD symptoms, and BMI of Greek patients with early- to midstage PD.

## Methods

### Study Design

This is a single-centered 3-arm crossover and open-label randomized controlled trial (in-person DfPD vs online DfPD vs control) of UPGRADE-PD (Upbeating Greek Application of Dance in Parkinson’s Disease). Blinding among participants and researchers is not possible due to the nature of the study. There are 6 possible research sequences, as shown in Table 1, and 3 possible carryover effects (1, 2, and 3) for each period from the prior intervention, as shown in Table 2. The study will last 10 months for each participant, including three 2-month research periods and two 2-month washout periods. Assessments will be conducted at enrollment (T_−0_=week −1), baseline periods (T_0_=week 0, T_2_=week 18, and T_4_=week 36), and postinterventional periods (T_1_=week 9, T_3_=week 27, and T_5_=week 45), as shown in Table 3. Allocation to each of the 6 possible sequences will occur after the completion of the first baseline assessment, as shown in the participant flow in Figure 1.

**Table 1 table1:** The UPGRADE-PD (Upbeating Greek Application of Dance in Parkinson’s Disease) study design.

Sequence	Period		
	First	Second	Third
ABC	A^a^	B^b^	C^c^
BCA	B	C	A
CAB	C	A	B
ACB	A	C	B
BAC	B	A	C
CBA	C	B	A

^a^Intervention A (in-person Dance for Parkinson’s Disease combined with usual medical care).

^b^Intervention B (online Dance for Parkinson’s Disease combined with usual medical care).

^c^Control group (usual medical care without Dance for Parkinson’s Disease).

**Table 2 table2:** The UPGRADE-PD (Upbeating Greek Application of Dance in Parkinson’s Disease) study’s code for the possible carryover effect.

Sequence	First period		Second period		Third period	
	Trial	Carryover effect	Trial	Carryover effect	Trial	Carryover effect
ABC	A^a^	0^b^	B^c^	1^d^	C^e^	2^f^
BCA	B	0	C	2	A	3^g^
CAB	C	0	A	3	B	1
ACB	A	0	C	1	B	3
BAC	B	0	A	2	C	1
CBA	C	0	B	3	A	2

^a^Intervention A (in-person Dance for Parkinson’s Disease combined with usual medical care).

^b^Noneffect.

^c^Intervention B (online Dance for Parkinson’s Disease combined with usual medical care).

^d^Effect from intervention A.

^e^Control group (usual medical care without Dance for Parkinson’s Disease).

^f^Effect from intervention B.

^g^Effect from the control group.

**Table 3 table3:** The UPGRADE-PD (Upbeating Greek Application of Dance in Parkinson’s Disease) schedule of enrollment, interventions, and assessments for participants.

Time point (wk)		Study period									
		Enrollment (T_–0_=wk –1)	Baseline 1 (T_0_ =wk 0)	Allocation (T_0_ =wk 0)	Postintervention 1 (T_1_ =wk 9)	Wash-out 1 (T_1_ =wk 9)	Baseline 2 (T_2_ =wk 18)	Postintervention 2 (T_3_ =wk 27)	Wash-out 2 (T_3_ =wk 27)	Baseline 3 (T_4_ =wk 36)	Postintervention 3 (T_5_ =wk 45)

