Procedures that will be performed during the study.The assessment is structured, for research reasons; it is characterized by empathy, and includes multiple movement and nonmovement aspects of Parkinson disease (PD), giving a full informative description of the study’s procedures and goals to participants by the main researcher (ME), who is a specialized neurological diseases physiotherapist, and an adapted physical and dance educator. Although ME is responsible for the whole communication with patients, assessments before and after each research period will be performed by an independent researcher who is specialist in the use of the specific tools to eliminate possible detection bias. Part of the assessment (Movement Disorder Society–sponsored revision of the Unified Parkinson’s Disease Rating Scale [MDS-UPDRS] and Montreal Cognitive Assessment [MoCA] tests) will be performed by specialized neurologists of the Eginition Neurological Outpatient Clinic (domains 1 and 3).Each step of the assessment procedure before and after each research period is explained; the necessity that each patient gives continuous feedback about possible adverse events is emphasized (domain 2).Translated and validated scientific tools are used, and a continuous multidisciplinary scientific collaboration between physicians, nurses, and physiotherapists is ensured as part of this study (domain 3).Therapeutic intervention goals were based on past research; however, personal patient needs were adapted in the dance combination’s design, based on our past pilot study [45], while individual music preferences were considered for the dance intervention’s design [66] (domain 4).A high-confidence environment, accompanied by emotional support, empathy, and respect between participants and the physiotherapist, will be ensured (domain 5).Although the early- to midstage severity stage of PD of participants usually does not demand specific modifications for each participant, due to the related motor independence with low fall risk [40], we are prepared to adapt our dance intervention following possible individual circumstances (domain 6).Dance for Parkinson’s Disease (DfPD) classes are generally characterized by supportive instruction in a way that participants feel free to perform each dance combination in their individual level of functionality [67]; thus, inclusion, adaptability, and accessibility to all are promoted during each dance class [68] (domain 7).The dance intervention is being conducted in a facility that is offered for free. Classes will be conducted solely by the main researcher (ME), while the trial will be partially funded by a charitable association, and continuous accessibility of patients to the research team will be provided (domain 8).

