**Balance**
Balance will be assessed before and after each research period by the Greek version [116] of Berg Balance Scale [117], which is a 14-item validated in PD [118] scale with a minimum score of 0, and a maximum score of 56, while lower scores indicate worse balance (0-20: high fall risk, 21-40: medium fall risk, and 41-56: low fall risk).

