**Movement and nonmovement PD symptoms**
Movement and nonmovement PD symptoms will be assessed before and after each research period by the Greek version of Movement Disorder Society–sponsored revision of the Unified Parkinson’s Disease Rating Scale (MDS-UPDRS) [122], which is a 4 parts scale. Part I assesses nonmotor experiences of daily living (13 items, score range: 0-52), part II assesses motor experiences of daily living (13 items, score ranges: 0-52), part III assesses motor signs (33 items, score ranges: 0-132), and part IV assesses motor complications, namely dyskinesias and motor fluctuations (6 items, score ranges: 0-24). Each item score ranges from 0 (normal) to 4 (severe), and higher scores indicate a greater impact of PD signs.

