### Recruitment

Recruitment started 6 months before the starting date of the program via relevant printed information material and health care practitioners (neurologists and nurses) of the Eginition University Hospital Neurological Outpatient Clinic. All study procedures have been discussed face-to-face individually with each potential participant before screening for eligibility by the primary researcher. The primary researcher (ME) has obtained written informed consent from the potential clinical trial participants before the study’s inclusion.

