### Data Collection and Management

All assessments will be conducted face-to-face by an independent investigator to eliminate possible detection bias, except of the Movement Disorder Society-Unified Parkinson’s Disease Rating Scale and Montreal Cognitive Assessment, which will be conducted face-to-face by specialized neurologists of the Eginition University Hospital Neurological Outpatient Clinic.

Participants are free to quit at any time if they wish to discontinue the study. In that case, reasons for withdrawal will be recorded, if this is possible. Participant’s enrollment will be followed by the research team’s assistance during the entire study period, including scheduling of data collection appointments, reminding of intervention’s appointments, and communicating the starting time of each research period.

Data, including consent forms, completed paper-based data files, and study notes, will be securely stored in the main investigator’s office, which will be locked. Raw data will be encrypted and stored digitally on a local computer with access rights to the main investigator. All original data will be archived for 5 years after the completion of the research and then destroyed, according to local regulations. All written data will be stored in a locked cabinet of the main investigator’s locked office for 5 years and then destroyed. Digital data will be stored on a password-protected local computer.

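### Blinding is ruled out for all researchers, yet an independent assessor who is nowhere said to be masked is relied on to prevent detection bias; the rater-scored secondary outcomes are exposed

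*Protocol article*

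**What the plan says.** Study Design describes a "single-centered 3-arm crossover and open-label randomized controlled trial" and adds: "Blinding among participants and researchers is not possible due to the nature of the study". The statement covers researchers as a whole.

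Two other places describe who measures the outcomes. Textbox 2, in the section on the patient-centered intervention, says that the assessments before and after each period "will be performed by an independent researcher who is specialist in the use of the specific tools to eliminate possible detection bias". Data Collection and Management says: "All assessments will be conducted face-to-face by an independent investigator to eliminate possible detection bias". It then excepts MDS-UPDRS and MoCA, "which will be conducted face-to-face by specialized neurologists of the Eginition University Hospital Neurological Outpatient Clinic".

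The Recruitment section names as one recruitment route the "health care practitioners (neurologists and nurses) of the Eginition University Hospital Neurological Outpatient Clinic".

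No section says that any assessor is kept unaware of sequence or current period, or that participants are asked not to reveal it at the visits.

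**The concern.** Detection bias arises when the person scoring an outcome knows, or can guess, which condition the participant has just been in. Using someone other than the instructor removes a personal stake in the classes, but it does not remove that knowledge. The article therefore gives a safeguard as its protection against detection bias that does not work through masking, next to a statement that researchers cannot be blinded at all.

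The reason given, the nature of the study, holds for participants and for the instructor. It does not hold for a separate assessor or for hospital neurologists who teach no classes. If the text is followed as written, balance, motor signs and cognition will be scored by people who are permitted to know whether the participant has just finished a dance period or a control period. A favourable tilt in those ratings would then look like a treatment effect.

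**Working it through.** No formula applies, and no figure in the plan depends on this point. The check is to set the statements side by side and then to sort the outcomes by who produces the score.

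**1. Who knows the allocation, and who needs to know it**

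- Participants: they know. This is unavoidable.
- Instructor: the main investigator teaches every class and handles all communication with patients (Intervention Description; Textbox 2). This is also unavoidable.
- Data analyst: performs the randomization and passes the group list in a sealed envelope to the principal investigator (Assignment of Interventions: Allocation).
- Independent assessor: has no role in teaching or allocation, and no need for the list is stated. Masking is not stated.
- Clinic neurologists (MDS-UPDRS, MoCA): they have no teaching role. Neither independence nor masking is stated. Neurologists of the same clinic helped to recruit.

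The stated obstacle to blinding therefore applies to the first two roles and not to the last two.

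**2. Which visits are exposed**

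There are six outcome assessments per participant, T0 to T5. Allocation follows completion of the first baseline assessment, so T0 is rated before any sequence exists. That leaves 6 − 1 = 5 assessments, T1 to T5, at which a rater could know the condition. All are face-to-face with a participant who knows it.

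**3. Which outcomes are exposed**

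| Outcome | Who produces the score | Would masking the assessor help? |
|---|---|---|
| PDQ-8 (primary) | Unblinded participant | No |
| PFS-16, MFIS, DASS-21, SARC-F | Unblinded participant | No |
| Berg Balance Scale | Independent assessor | Yes |
| MDS-UPDRS part III | Clinic neurologist | Yes |
| MoCA | Clinic neurologist | Yes |
| Grip strength, walking speed (used for sarcopenia and frailty status) | Instrument or timed test, run by the assessor | Somewhat, mainly through encouragement |

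For the first two judged scales the article says: "Balance will be assessed before and after each research period by the Greek version [116] of Berg Balance Scale", and "part III assesses motor signs (33 items, score ranges: 0-132". Everything in the lower half of the table is a secondary outcome.

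**4. Result**

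For the outcomes where an assessor could protect against detection bias, masking is not provided for. For PDQ-8 and the other self-reports, no arrangement of assessors could provide that protection, so the claim made for all assessments is too broad in any case.

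**The case against.** **The conflict may be one of wording.** Researchers in Study Design may mean only those who deliver the intervention, and the detection-bias phrase states a purpose, not a result. On that reading the sections do not strictly contradict each other, and masking details could sit in a fuller protocol. Part of this stands: the phrase is one of purpose, and separating assessor from instructor is a real partial safeguard. But the Study Design statement carries no such limit, and even on the narrow reading the named means does not serve the named purpose. This goes beyond a detail lost in condensing, because the article itself makes both statements.

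**The primary outcome is untouched.** This stands in full. A reader might infer that the trial's main conclusion is threatened by unmasked assessors. It is not: PDQ-8 is open to participant expectation in an open-label trial, which the article already declares, and masking assessors would not change that. Grip is measured with a calibrated digital dynamometer and walking is a timed test, so rater judgement has little room there.

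**The harm can be put as a false-positive rate.** A reader might take the correlation of 0.64 and the 40 participants, assume a rating bias, and compute how often a secondary outcome would be falsely significant at 5%. The document does not support this. The 0.64 is the sample-size assumption for quality of life, and no correlation is given for the Berg scale, MDS-UPDRS or MoCA. Secondary outcomes are to be Bonferroni-corrected (Statistical Analysis) over a number of tests that is not fixed there, so 5% is not the level at which they would be tested. No rating bias is given. Bonferroni correction does not remove bias, but any such rate would rest on invented inputs.

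**The rating neurologists already know the participants.** Eligibility requires that participants be patients of that clinic, with an attending physician's consent. It is tempting to conclude that the raters know the current period. The article does not say that the raters are the attending physicians or that they are told the period; it is only silent on masking.

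**Conclusion.** The point holds for the rater-scored secondary outcomes: Berg Balance Scale, MDS-UPDRS part III, MoCA and, less so, the grip and walking tests. The statement that researchers cannot be blinded is wider than its reason supports, and assessor independence is asked to do what only masking can do. The documents do not show that raters are in fact unmasked, and they do not show that any result will be biased. They show that nothing in the plan masks the raters.

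The size of the bias cannot be derived from the document, and I give none. The conclusion rests on two readings: that researchers in Study Design includes assessors, as the unqualified wording suggests, and that no unseen document already masks them. If either is wrong, the remedy reduces to a clarifying sentence. The change is worth making because it is cheap and uses assessors who are already in place.

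**What to change.** 1. In Study Design, limit the statement that blinding is not possible to participants and the instructor.
2. For all remaining visits, mask the independent assessor and the neurologists to sequence and current period. The allocation list should be held only by the data analyst, who randomizes, and the principal investigator, who receives it.
3. Ask participants before each visit not to disclose their current or recent condition, and record the assessor's guess of the condition at each visit.
4. Report which visits were rated unmasked.
5. Where masking was not done, withdraw the wording that detection bias is eliminated. In no case apply it to PDQ-8 or the other self-reports; describe these as reports by unblinded participants.

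Cost: an instruction to existing assessors and participants, one extra question per visit, and edits to three places in the text. No extra staff are needed. The limits should be stated openly. Some participants will reveal their condition anyway. Recruitment had closed and the trial was running when the article was submitted, so visits already made cannot be covered. Steps 1, 4 and 5 remain possible whatever stage the trial has reached.
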